**Figure 1 F1:**
[figure not shown]
Flow chart.

**Table 1 T1:** Study assessment procedures and timetable

**Assessment**	**Comparability of wards; interview**	**Baseline assessment**	**Six-month assessment**	**Twelve-month assessment**
Inclusion criteria, informed consent	X			
Demographics, diagnoses		X		
CDR		X		
MMSE		X	X	X
Verbal fluency, clock-drawing test		X	X	X
MNA		X		
Drug use		X	X	X
15D QOL measure		X	X	X
PWB scale		X	X	X
RAI assessment	X	X	X	X
Falls			X	X
Hospitalization, use of health and social services, mortality				X
X				

CDR, clinical dementia rating scale (Hughes et al. 1982); MMSE, Mini Mental State Examination (Folstein et al. 1972); MNA, Mini Nutritional Assessment (Guigoz et al. 2002); 15D, health-related quality of life scale (Sintonen et al. 1990); PWB, psychological well-being scale (Routasalo et al. 2009); RAI, Resident Assessment Instrument (Morris et al. 2000).

Drug use will be assessed as the point prevalence on the day of assessment. Residents will be classified as regular drug users if their medical charts indicate a regular sequence of administration on a daily basis. Additional analyses will be performed including both regularly used drugs as well as drugs used on a *pro re nata* (*prn*, or as needed) basis. The drugs administered to residents will be classified according to the anatomical therapeutic chemical (ATC) classification system recommended by the World Health Organization (WHO)
[44]. The drugs that will be considered as inappropriate, having anticholinergic properties or being psychotropic drugs are presented in Additional file
1: Table S1. The total number of these drugs each resident is using one, on a regular daily basis and two, both regularly or *prn* will be counted.

We randomized wards instead of individual participants in order to avoid contamination. The wards selected for this study were all using the Minimum Data Set (MDS)/Resident Assessment Instrument (RAI) version 2.0 for home care

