[45]. MDS is used for assessing the residents’ needs and for individual care planning purposes. Each nurse has been educated to use MDS, and the assessment is routinely performed twice annually or whenever there is a substantial change in the resident’s status. In addition to the internationally well-validated scales and items, MDS provides a patient’s ward profile, often called ‘the case-mix’ (for example, ‘psychogeriatric’, ‘physically disabled’ or ‘cognitively impaired’), and gives the mean level of residents’ need for assistance. After identifying the case-mix in each of the wards, the wards will be divided into dyads having approximately the same characteristics. These dyads will be further randomized, by means of computer-generated random numbers, into two arms: those to receive staff training or to receive education after the trial. In addition, individual RAI items (for example, the proportion of fallers) and some of the well-validated RAI scale items (for example, neuropsychiatric symptoms, symptoms of delirium) will be used in measuring the effects of intervention.

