### **Intervention**

In intervention wards, the nurses and consultant physician, if available, will receive training with emphasis on drug safety, inappropriate drugs for older people, drugs with anticholinergic properties, problems related to psychotropic drugs and the adverse effects related to NSAIDs and PPIs. D-class interactions of drugs will be discussed. We will also give information in these educational sessions about evidence-based treatments in this patient group. The training will be organized as an activating discussion session separately for each intervention ward. Cases related to their own residents will be discussed. Two educational sessions per ward will be organized. In addition, nurses responsible for pharmaceuticals will be provided with more intensive training, together with others responsible for drugs, regarding procedures and processes of how to reduce drug use. A list of inappropriate drugs will be provided to all nurses working in intervention wards. In addition, for each intervention ward a nurse responsible for drugs will be appointed. She/he will bring potential drug problems to the consulting physician in assisted living. In institutions, assisted living facilities and nursing homes in Helsinki, physicians act as visiting consultants to whom the nurses take problematic cases. The physician will take the final responsibility to change or to continue the drugs.

The control wards will continue with the usual care processes. The staff in these wards will receive training in drug treatment after the study is over.

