### **Statistical analyses**

Required sample size calculation is based upon the change in the proportion of users of inappropriate, anticholinergic or psychotropic drugs. Sample size was calculated as follows: if in the control group 36% use inappropriate drugs, the minimum group difference with the assessment is 20%, type I error 5%, power 80%, which results in 106/group. Because we recruit participants from wards and aim to include as many as possible from those wards, the final sample size may differ slightly from this figure.

In these baseline findings, for the continuous variables, descriptive values will be expressed by means with standard deviations (SD) and medians with range. For the variables with a normal (Gaussian) distribution, statistical comparisons between the groups will be made by using a *t* test. If the variables have a non-normal distribution or ordinal level, statistical comparison between groups will be performed with the Mann Whitney *U* test. Measures with a discrete distribution will be expressed as percentages (%) and analyzed by *X*^2^ or Fischer’s exact test when appropriate.

The results will be analyzed according to intention to treat. For imputation method, ‘the last observation carried forward’ (LOCF) and ‘worst-rank score’ principle will be used. For the most important outcome parameters, estimation of confidence interval (95%) will be used in addition to testing. Since the distributions of health care costs are highly skewed, the differences between means and confidence intervals are estimated using the bootstrap method (bias corrected and accelerated bootstrapping).

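### Wards are randomised in matched dyads, but the only between-group tests named treat residents as independent, and no described analysis mentions ward or dyad

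*Protocol article*

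**What the plan says.** **Design.** The Study procedures section gives the unit of randomisation: "We randomized wards instead of individual participants in order to avoid contamination". After case-mix has been identified, "the wards will be divided into dyads having approximately the same characteristics", and then "These dyads will be further randomized, by means of computer-generated random numbers, into two arms".

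**Intervention.** It is delivered to wards. The Intervention section says "The training will be organized as an activating discussion session separately for each intervention ward". It also provides for an appointed nurse responsible for drugs on each intervention ward, who takes problems to the consulting physician.

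**Analysis.** The Statistical analyses section names these between-group methods:

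- The t test, where data are Gaussian. The sentence runs "For the variables with a normal (Gaussian) distribution, statistical comparisons between the groups will be made by using a" and closes by naming that test.
- The Mann-Whitney U test, where data are ordinal or not Gaussian.
- The chi-square test, or Fisher's exact test, where data are discrete.
- 95% confidence intervals, alongside testing, for the most important outcomes.
- For health care costs, "the differences between means and confidence intervals are estimated using the bootstrap method", in its bias-corrected and accelerated form. The unit to be resampled is not stated.

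The paragraph with the three tests opens with a phrase tying it to baseline findings. The next paragraph concerns outcomes (intention to treat, imputation, intervals, bootstrap). It refers to testing but names no test. No ward or dyad term, intracluster correlation or design effect appears anywhere. The section mentions wards only to explain why the final sample size may differ slightly from the calculated one.

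**The concern.** In their standard form, the t, Mann-Whitney, chi-square and Fisher tests take each resident as an independent observation. Here the independent units are the wards, paired in dyads. The primary outcomes are measures of drug use, and residents of a ward share nurses and, through them, a route to the prescriber. Some positive within-ward correlation is therefore likely, and the training itself can add to it, because each ward is trained separately.

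If between-ward variance is left out of the standard error, the 5% type I error and the 95% coverage need not hold for either primary outcome. The Discussion presents the intervention as easy to implement if effective, so a false positive could have practical consequences.

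**Working it through.** **1. The plan's own figure.** The sample size section gives 36% in controls, a difference of 20% (read as percentage points), type I error 5%, power 80% and 106 per group. The usual two-proportion formula for independent subjects, two-sided, with 36% against 56%, is

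n = [1.960·√(2·0.46·0.54) + 0.842·√(0.36·0.64 + 0.56·0.44)]² / 0.20² = 96.3.

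With the continuity correction, n′ = (n/4)·[1 + √(1 + 4/(n·0.20))]² = 106.06. This is 106 to the nearest whole number, or 107 rounded up. The stated figure is thus matched by a formula for individually randomised subjects with no design effect, which suggests that clustering was not considered there either. (For a fall from 36% to 16%, the same formulas give 75, or 85 with the correction.)

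**2. Inputs that are assumptions.** The article gives neither the number or size of wards nor an intracluster correlation (ICC). I take m = 10 or 15 participants per ward and ICC = 0.02, 0.05 or 0.10.

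**3. No gain from matching (upper end).** The design effect is DE = 1 + (m − 1)·ICC. A nominal 5% test then has true type I error 2·[1 − Φ(1.96/√DE)], and the naive interval has 1/√DE of its correct width.

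| m | ICC | DE | True type I error | Naive interval width / correct width |
|---|---|---|---|---|
| 10 | 0.02 | 1.18 | 7.1% | 0.92 |
| 10 | 0.05 | 1.45 | 10.4% | 0.83 |
| 10 | 0.10 | 1.90 | 15.5% | 0.73 |
| 15 | 0.02 | 1.28 | 8.3% | 0.88 |
| 15 | 0.05 | 1.70 | 13.3% | 0.77 |
| 15 | 0.10 | 2.40 | 20.6% | 0.65 |

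**4. Partial gain from matching.** Let s be the share of between-ward variance common to the two wards of a dyad. That share cancels in the difference between arms, so the variance ratio becomes DE(s) = 1 − ICC + m·ICC·(1 − s). With s = 0 this is the design effect in step 3.

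| Setting | s = 0 | s = 0.5 | s = 0.8 | s = 1 |
|---|---|---|---|---|
| m = 10, ICC 0.05: DE(s) | 1.45 | 1.20 | 1.05 | 0.95 |
| True type I error | 10.4% | 7.4% | 5.6% | 4.4% |
| m = 15, ICC 0.10: DE(s) | 2.40 | 1.65 | 1.20 | 0.90 |
| True type I error | 20.6% | 12.7% | 7.4% | 3.9% |

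Simulating the t test with 10 wards of 10 per arm and ICC 0.05 gave 0.107, 0.075, 0.054 and about 0.05, in line with the first setting.

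**5. Break-even.** DE(s) = 1 when m·(1 − s) = 1, so s = 1 − 1/m: 90% for m = 10 and 93% for m = 15. Below that share the naive test is anti-conservative; above it, slightly conservative.

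**The case against.** **The tests may be meant for baseline only.** Read literally, the opening of the paragraph assigns them to baseline comparisons, and an unseen analysis plan could hold the outcome model. The ambiguity is real. It does not remove the point: the outcome paragraph relies on testing and names nothing else, and the sample size follows the same individual-level logic. The article is also specific elsewhere, down to the imputation rule and the bootstrap variant, so this is a mismatch with the design rather than detail left out for brevity.

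**The bootstrap.** A reader might infer that the cost bootstrap also assumes independent residents. The article does not support that. The resampling unit is not stated, and a bootstrap can resample wards or dyads. What stands is that it is not said to do so.

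**Matching.** A reader might infer that the p-values are bound to be too small. That does not follow either, since step 4 shows the error shrinking as dyads share more ward variance. But pairing is on approximately similar case-mix, and the article does not say that wards were matched on prescriber or prescribing habits. A shared part of about 90% or more is a strong assumption. Even then the unmatched tests would be slightly conservative and would waste the precision that matching bought.

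**Size of the correlation.** Physicians are visiting consultants, and the article does not say that each ward has its own. Staff may move between sites. One primary outcome is a change in drug number, which removes stable ward differences. Each could lower the ICC. That bears on size; any positive correlation not largely absorbed by the dyads still causes the error.

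**Conclusion.** The point holds in conditional form. The design randomises wards within dyads, the only tests named are resident-level tests, and no described analysis mentions ward or dyad. Applied to residents' outcomes, those tests overstate the evidence if there is positive within-ward correlation that the matching does not largely absorb.

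The size cannot be fixed from the article. The range of about 7% to 21% rests on assumed ward sizes of 10 to 15, an assumed ICC of 0.02 to 0.10 and no benefit from matching, so it is an upper end for those inputs and not an estimate. With matching that explains half the ward variance, the two settings in step 4 give 7.4% and 12.7%; with nearly all explained, about 5% or slightly below.

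It should be corrected before outcomes are analysed, because it bears on the validity of both primary comparisons.

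**What to change.** State that all outcome comparisons and confidence intervals account for the ward as the randomised unit and for the dyad. Two routes would do:

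- A mixed model or GEE with ward clustering and dyad as a factor (logistic for the proportion, linear or count for the number of drugs), with a small-number-of-clusters correction suited to the actual number of wards.
- If wards are few, a paired dyad-level analysis of ward summaries.

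State also that the cost bootstrap resamples wards or whole dyads. Say plainly that the t, Mann-Whitney, chi-square and Fisher tests are for baseline description only, if that is the intention.

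**Cost.** Changed wording and slightly more analysis work, with no new data. Intervals will usually be wider and power lower at the fixed sample size. With m = 10, ICC 0.05 and no gain from matching, for example, 106 residents per arm carry the information of 106/1.45 ≈ 73 independent ones. That loss comes from the design; the resident-level tests only hide it.

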### **Study procedures**

The baseline study visit lasts about one hour and includes an interview to ascertain residents’ demographic data, diagnoses, and medications used. The diagnoses and medications are confirmed from medical records.

The participant will be assessed using the clinical dementia rating scale (CDR)
[37], Mini Mental State Examination (MMSE)
[36], verbal fluency
[38,39], the clock-drawing test
[40], and Mini Nutritional Assessment (MNA)
[41]. Patients’ psychological well-being will be assessed using the psychological well-being (PWB) scale
[42] and health-related quality of life (HRQOL) will be assessed by 15D measure
[43]. Participants will be assessed by two study nurses three times during the year: at baseline, and at six and twelve months. The flow chart of the study is presented in Figure
1, and study assessment procedures are described in Table
1. Hospitalizations, use of other health and social services and death dates will be retrieved from the central registers for one year from baseline measurements.

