### **Outcome measurements**

The research nurses perform their assessments at zero, six and twelve months.

Primary outcome measures are:

· the proportion of persons using inappropriate, anticholinergic or more than two psychotropic drugs (these drugs are presented in Additional file
1: Table S1), and

· the change in the mean number of inappropriate, anticholinergic and psychotropic drugs.

Secondary outcome measures are:

· change in the mean WHO-defined daily dose
[44] of inappropriate, anticholinergic or psychotropic drugs

· the proportion of persons with significant drug-drug interactions according to SFINX
[27]

· the number of drug-related problems
[46]

· change in the mean number of drugs

· change in the proportion of participants having nine or more drugs

· use of health care services and their costs during a 12-month follow-up

· the number of hospitalizations/follow-up time

· the 15D HRQOL measure
[43]

· cognition according to verbal fluency and clock-drawing test
[38-40], and CDR sum of boxes
[37]

· change in neuropsychiatric symptoms or symptoms of delirium according to the RAI instrument
[45], and

· the number of fallers according to the RAI instrument
[45].

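### Adjusting both primary drug-use outcomes for baseline drug use, which is already collected, would gain precision at no cost; the protocol names only unadjusted tests

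*Protocol article*

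**What the plan says.** Under Outcome measurements, the protocol article lists two primary outcomes. The first is "the proportion of persons using inappropriate, anticholinergic or more than two psychotropic drugs". The second is "the change in the mean number of inappropriate, anticholinergic and psychotropic drugs". The first has no baseline term. The second uses baseline only by subtraction.

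Under Statistical analyses, the paragraph that names group tests opens: "In these baseline findings, for the continuous variables, descriptive values will be expressed by means with standard deviations (SD) and medians with range". It then assigns tests by type of variable:

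- Normal variables: "statistical comparisons between the groups will be made by using a" t test.
- Other continuous or ordinal variables: "If the variables have a non-normal distribution or ordinal level, statistical comparison between groups will be performed with the Mann Whitney" U test.
- Categorical measures: "Measures with a discrete distribution will be expressed as percentages (%) and analyzed by" chi-square or Fisher's exact test.

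The next paragraph, on results, covers intention to treat, imputation, 95% confidence intervals for the most important outcomes, and a bootstrap for costs. It names no test, model or covariate for the drug outcomes.

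Baseline drug use is available. Study procedures places it in the baseline interview and adds: "The diagnoses and medications are confirmed from medical records". Table 1 schedules drug use at baseline, six and twelve months, and the text after it says: "Drug use will be assessed as the point prevalence on the day of assessment". The same section describes wards grouped into dyads by case-mix and mean need for assistance. Drug use is not named as a matching factor.

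**The concern.** A resident's drug list at baseline is likely to predict the list a year later. A raw follow-up proportion leaves that information unused. A change score uses it with a fixed coefficient of one, which is less efficient than letting the data set the coefficient. Because the dyads are not matched on drug use, a chance difference in baseline use between arms is not directly controlled.

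The rule for choosing a test raises a second issue. The second primary outcome is worded as a mean. Drug counts are integers, so normality holds at best approximately. If a distribution check sends the count to Mann-Whitney, the test no longer addresses a difference in means, and the quantity being compared depends on the observed data.

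At stake is power in a trial whose own Discussion warns that deaths may reduce power and that contamination may shrink the difference between arms.

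**Working it through.** **The plan's own figure.** The inputs are a 36% control rate, a 20% difference, type I error 5%, power 80% and 106 per group (Statistical analyses). The usual two-proportion formula, taken two-sided, is

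n = [1.960·√(2p̄(1−p̄)) + 0.842·√(p₁(1−p₁) + p₂(1−p₂))]² / (p₁−p₂)²

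- 36% against 56%: n = 96.3, and 106.1 with continuity correction (107 after rounding up). This matches the stated 106.
- 36% falling to 16%: n = 74.3, and 84.0 with correction (75 and 85 after rounding up). This does not match.

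On either reading the calculation compares two unadjusted proportions, so it contains no gain from baseline adjustment.

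**Gain for the count outcome.** Let σ² be the variance of the count (equal at both times), r the baseline-to-follow-up correlation, and n the number per arm. The variance of the estimated difference is:

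- change score: (2σ²/n)·2(1−r)
- baseline as covariate (ANCOVA): (2σ²/n)·(1−r²)

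The ratio is (1−r²)/[2(1−r)] = (1+r)/2, so the reduction is (1−r)/2. The documents do not give r, so 0.5 to 0.8 is assumed.

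| r | Ratio (1+r)/2 | Reduction | n equivalent to 106 | Power if change score has 80% |
|---|---|---|---|---|
| 0.5 | 0.75 | 25% | 79.5 → 80 | 89.9% |
| 0.6 | 0.80 | 20% | 84.8 → 85 | 87.9% |
| 0.7 | 0.85 | 15% | 90.1 → 91 | 86.0% |
| 0.8 | 0.90 | 10% | 95.4 → 96 | 84.0% |

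Power is Φ[(1.960 + 0.842)/√((1+r)/2) − 1.960]. All rows treat residents as independent.

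**Binary outcome.** The documents give no association between baseline and follow-up status, and the formula above is for a continuous outcome. No gain is computed.

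**Scale of chance baseline differences (illustration).** At 36% and 106 per arm, the SD of the difference between arms is √(2·0.36·0.64/106) = 0.066 with independent residents. With an assumed design effect of 1.45 (for example 10 residents per ward and an intraclass correlation of 0.05: 1 + 9·0.05), it is √(2·0.36·0.64·1.45/106) = 0.079. This is 6.6 to 7.9 percentage points, against 20 points if the stated difference is absolute. Two limits apply. In the Background, 36% refers to Beers-list drugs alone and not to the composite. Matching on case-mix may also reduce the spread.

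**The case against.** The strongest objection is that the named tests do not govern the primary outcomes, because their paragraph is about baseline findings. The results paragraph leaves the tests for the drug outcomes open, and a condensed article may leave model form and covariates to an analysis plan that is not shown. This stands in part. The protocol does not assign these tests to the outcomes, and a missing model alone would not be a finding. What remains is what the article does fix: a raw proportion and a change score as the primary quantities, with no other group test named for them.

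A reader might infer that both primary outcomes will be compared by t or Mann-Whitney tests. That is not supported. On the protocol's own scheme a proportion goes to chi-square or Fisher's exact test; only the count could go to the other two.

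A reader might also infer that the unadjusted comparison is biased, through baseline imbalance in the proportion or over-correction in the change score. That is not supported either. Under randomisation both are unbiased on average. Conditional on a baseline gap g in the mean count, a raw follow-up difference carries about r·g of it and a change score about −(1−r)·g, but across randomisations this is sampling error.

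It is also tempting to say that imbalance is likely because wards are few, or that the counts are small and skewed. The protocol states neither.

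Two further points are fair. The sample-size sentence speaks of a change in the proportion of users, so baseline may be meant to enter the first outcome; the outcome list does not say so. The protocol also promises confidence intervals for its key outcomes, so it cannot be said that no interval is planned. It does not say which quantity the interval will describe if the test is a rank test.

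**Conclusion.** The point holds as a free improvement in efficiency, and not as an error that invalidates the comparison. For the count outcome, replacing the change score with a baseline-adjusted analysis cuts variance by about 25% at r = 0.5 and 10% at r = 0.8. The gain shrinks as drug use becomes more persistent. These figures rest on an assumed r, equal variances at the two times and independent residents. The proportion makes no stated use of baseline and should also benefit, but the documents do not allow the gain to be sized.

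Separately, a normality-driven switch to Mann-Whitney would not estimate the mean that the second outcome names. Whether the protocol intends that switch for the outcomes is an inference from its being the only rule given.

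**What to change.** State one analysis for each primary outcome, here taken at 12 months, the last assessment:

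1. **Composite:** a logistic mixed model or GEE for 12-month status, with baseline composite status as a covariate. Report the adjusted difference in proportions, standardised from the model, with a 95% confidence interval.
2. **Drug count:** an ANCOVA-type mixed model, or a Poisson or negative binomial model with robust errors, for the 12-month count, with baseline count as a covariate in place of the change score. Report the adjusted mean difference with a 95% confidence interval.
3. **Design:** account for ward and dyad in both models. A baseline covariate in a resident-level test would not by itself give a valid analysis.
4. **Test choice:** drop the distribution-dependent switch for the count outcome, and say explicitly whether the listed tests apply to the baseline comparison only.

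The worst-rank imputation in the same section is designed for rank comparisons, so the text should also say how such residents enter a comparison of means.

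The cost is analysis wording only. No new data, visits or participants are needed.

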## **Discussion**

This rigorous randomized trial will test whether a relatively light educational intervention will have an effect on the use of inappropriate, anticholinergic and psychotropic drugs use among frail older residents in assisted living facilities. The drugs considered in this trial include a wide variety of potentially harmful drugs that have been shown in recent years to have adverse effects in this particular patient group. Intervention is pragmatic in nature, and its potential effects rely on those professionals who actually work with these older people. The nurses will be trained to identify the harmful drugs, whereas the final decision to stop these medications will be made by physicians consulting to these wards. Thus, if the intervention proves to be effective, it can be implemented easily.

The strength of this study is its pragmatic nature and easily implemented training. Thus, the findings should be applicable in real life. The population is frail and vulnerable and, according to our previous studies, uses a high number of these drugs. Thus, the floor effect is not easily reached in the primary endpoint. Besides the number of potentially harmful drugs, this study will also examine the effects of intervention on residents’ QOL. Contrary to many previous trials, this study will also collect data on participants’ hospitalizations. Inappropriate drugs according to Beers, anticholinergic drugs, as well as psychotropic drugs have been suggested to increase hospitalizations and complications
[16,19,23,25].

However, there are also potential limitations in this study. First, the population is old and frail with many comorbidities, and, thus, vulnerable to competing causes of complications and deaths. This may decrease the power of the study. The second challenge relates to a sufficient difference to be attained between the groups with our intervention. Contamination might be a problem, because the staff changes rapidly in these institutions and they may also move from intervention site to control site. The staff is also stressed, and it is unclear how they will accept our training. In addition, the staff will also learn about evidence-based treatments in this patient group (such as the beneficial effects of vitamin D, stroke prevention, dementia drugs, pain treatment), which may increase the number of medications, and, thus, may even have effects in the opposite direction from that intended in this study.

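### LOCF and worst-rank imputation suit the drug-use primary outcomes poorly: with equal loss both dilute the effect, and observed data while alive would serve better

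*Protocol article*

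**What the plan says.** The Statistical analyses section specifies an intention-to-treat analysis and then sets the handling of missing values: "For imputation method, ‘the last observation carried forward’ (LOCF) and ‘worst-rank score’ principle will be used". It does not say which rule applies to which outcome, or to death as against other loss.

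Under Outcome measurements, the first primary outcome is binary at the level of the resident: "the proportion of persons using inappropriate, anticholinergic or more than two psychotropic drugs". The second rests on a count per resident and is given as "the change in the mean number of inappropriate, anticholinergic and psychotropic drugs". On timing, "The research nurses perform their assessments at zero, six and twelve months". The Study procedures section adds that "Drug use will be assessed as the point prevalence on the day of assessment", so no value exists after death or loss.

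The Discussion describes the residents as "vulnerable to competing causes of complications and deaths. This may decrease the power of the study". Participants need an estimated prognosis of more than six months, while the trial runs for twelve. Death dates are to be taken from central registers (Study procedures). No death or dropout rate is given, and the 106 per group carries no stated allowance for loss.

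**The concern.** Both rules are single imputation: one filled-in value per missing record, then analysed as if it had been observed. For drug use each has a further problem.

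- **LOCF.** A resident lost or dead before the six-month visit has only a baseline value. Carrying it to month 12 records no change, which in the intervention arm means no effect of training. For a resident who died, it also assigns drug use to someone who was taking nothing. Residents lost after month 6 carry a post-training value, so the problem is smaller for them.
- **Worst-rank.** Scoring a death as the worst result makes that resident a user of harmful drugs, whatever the charts showed. The drug-use outcome then becomes partly a mortality outcome.

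At stake are the size of the primary contrast, the power to detect it and, if loss truly differs between arms, its direction.

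**Working it through.** **Inputs from the article (Statistical analyses):** control rate 36%, difference 20%, type I error 5%, power 80%, 106 per group. **Assumptions:** the difference is in percentage points and in the intended direction (36% versus 16%); the test is two-sided; baseline use is 36% in both arms and stays so in controls; a share m is lost equally in both arms, before month 6 for the LOCF case; clustering by ward is ignored.

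**The plan's own figure.** The pooled two-proportion formula gives 107 per group for 36% versus 56% with continuity correction (97 without), which matches 106. For 36% versus 16% it gives 75 (85 with correction), so 106 per group has more than 80% power in the intended direction. That mismatch is a separate matter; it only explains why the starting power below is 92%.

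**Rates at month 12**
- LOCF: intervention (1 − m) × 0.16 + m × 0.36; control 0.36.
- Worst-rank: intervention (1 − m) × 0.16 + m; control (1 − m) × 0.36 + m.
- Observed residents: 0.16 and 0.36, with n = 106 × (1 − m).

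Under both rules the difference is (1 − m) × 0.20. It would be the same if deaths were scored worst and other early losses carried forward, because the filled-in part is then equal in both arms and cancels.

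**Power** = Φ{[d − 1.96 √(2p̄(1 − p̄)/n)] / √([p₁(1 − p₁) + p₂(1 − p₂)]/n)}, where d is the difference and p̄ the mean of the two rates.

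- No loss: (0.20 − 1.96 × 0.0603)/0.0587 = 1.40, power 92%.
- LOCF, m = 20%: intervention 0.8 × 0.16 + 0.2 × 0.36 = 0.200; (0.16 − 1.96 × 0.0617)/0.0607 = 0.64, power 74%.
- Worst-rank, m = 20%: 0.8 × 0.16 + 0.2 = 0.328 and 0.8 × 0.36 + 0.2 = 0.488; (0.16 − 1.96 × 0.0675)/0.0666 = 0.42, power 66%.

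| Loss m | Difference, either rule | LOCF rates | LOCF power | Worst-rank rates | Worst-rank power | Observed-resident power (20 points) |
|---|---|---|---|---|---|---|
| 10% | 18 points | 18% vs 36% | 84% | 24.4% vs 42.4% | 80% | 89% (n = 95.4) |
| 20% | 16 points | 20% vs 36% | 74% | 32.8% vs 48.8% | 66% | 85% (n = 84.8) |
| 30% | 14 points | 22% vs 36% | 61% | 41.2% vs 55.2% | 53% | 80% (n = 74.2) |

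The LOCF columns are an upper limit on dilution, since losses after month 6 carry a post-training value. The worst-rank columns hold whenever the death occurs.

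**Unequal loss, no drug effect (36% in both arms).** With 20% lost in one arm and 10% in the other, worst-rank gives (0.8 × 0.36 + 0.2) − (0.9 × 0.36 + 0.1) = 0.488 − 0.424 = 6.4 points. LOCF gives 0 while use is stable; if use fell from 36% to 26% in both arms it would give (0.8 × 0.26 + 0.2 × 0.36) − (0.9 × 0.26 + 0.1 × 0.36) = 1 point.

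**Equal true mortality, no drug effect.** In a simulation with 15% expected deaths in both arms, 106 per arm and no clustering, worst-rank rejected in about 4.6% of trials, within the nominal 5%.

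**The case against.** The strongest reply is that the article is condensed. Which rule serves which outcome may well stand in a fuller document, and its absence here is no fault. That is accepted: the point concerns the methods the article does commit to, not the missing assignment.

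Four stronger readings are tempting, and the article does not support them.

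- *The two rules contradict each other.* A resident who had stopped a drug by month 6 and then died is a non-user under LOCF and a user under worst-rank, but only if both rules are applied to the same record. Worst-rank for deaths and LOCF for other loss, or worst-rank for outcomes such as 15D, fits the sentence equally well. The rules also agree for anyone last seen as a user.
- *Both are declared the main method for drug use.* The sentence neither says so nor names the drug-use outcomes.
- *Losses will be common and mostly deaths.* The Discussion calls residents vulnerable and says power may fall; it gives no rate. The prognosis criterion is meant to limit deaths before month 6, where LOCF does most harm.
- *Any chance imbalance in deaths becomes a false drug effect.* It does not; type I error is kept. A 20% versus 10% split at 106 per arm would itself be unusual by chance (p about 0.04), and the resulting 6.4 points has p about 0.35. Bias needs a true difference in mortality or loss.

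It is also fair that at 10% loss both rules still leave about 80% power or more, that dilution is conservative for a superiority claim, and that the observed-resident column assumes the lost residents would have shown the full effect. An analysis of residents while alive conditions on an event after randomisation and rests on an untestable assumption. These points limit the size of the concern; they do not make either rule a good description of drug use.

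**Conclusion.** The concern holds in a limited form. The article commits to two single-imputation rules that suit the drug-use outcomes poorly: LOCF because it records no change for residents with no six-month visit, worst-rank because it would count a death as harmful drug use. With equal loss the consequence is dilution, not a false positive: 2, 4 or 6 of the 20 points at 10, 20 or 30% loss. Compared with using observed residents, the power cost is 5, 11 or 19 percentage points under LOCF and 9, 19 or 27 under worst-rank.

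These sizes rest on assumed loss rates, on all LOCF losses falling before month 6, on loss unrelated to the effect, and on ignoring clustering. With low or late loss the cost is modest. This is a worthwhile and cheap improvement to a stated method, not an internal contradiction in the plan.

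**What to change.** - For the two drug-use primary outcomes, make the primary analysis a likelihood-based repeated-measures model on all observed values at 0, 6 and 12 months, suited to the binary and the count outcome respectively.
- Do not impute drug use after death. State that the result describes residents while alive, and report deaths by arm beside it from the register data.
- Keep LOCF and worst-rank as labelled sensitivity analyses. Limit worst-rank to outcomes where death is a meaningful worst state, such as health-related quality of life.

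The cost is revised wording and modest extra analysis. No new data are needed, because the three assessments and the death dates are already planned. The downside is small but real: the result rests on data being missing at random and refers to residents while alive, so the sensitivity analyses should be shown next to it.
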